### Comparison group

Mothers from the comparison groups will receive all the education materials and menus used in the programme. In order to encourage continued participation and to prevent dropouts from the comparison group during the 3-month programme, incentives will be provided for children who complete the anthropometric measurements and mothers who return the completed questionnaire during each follow-up.

### Training of volunteers

Volunteers (mothers of well-nourished children) will be recruited from PD families that are identified in the initial phase. Fifteen or more volunteers will be recruited. They will play a main role in conducting the peer-led cooking session and actively supporting the participating mothers of the intervention group from the NPD family to acquire a new skill. A few discussions will be conducted with the volunteers to equip them with the necessary knowledge and skills so that can lead the cooking demonstration and help the participating mothers.

### Measurements

All the measurements in the study will be taken at the baseline, immediate post-intervention, and 3-month post-intervention for both intervention and comparison groups. A Malay language self-administered questionnaire on sociodemographic characteristics, nutritional knowledge, and food security status will be answered by mothers. The sociodemographic background of the mother-child dyads will be self-reported by the mothers, including information on both the child and the mother.

#### Primary outcome

Anthropometric measurements of the children will be performed by the researcher. The height of the children will be measured to the nearest 0.1 cm by using a SECA Body Meter 213 (SECA, Germany). Weight will be measured to the nearest 0.1 kg by using a TANITA Digital Weight Scale HD662 (TANITA Corporation, Japan). The collected anthropometric data will be entered and analysed by using the WHO Anthro Survey Analyser [41]. Z-score for weight-for-age (WAZ) will be calculated and underweight (WAZ<-2 SD) children will be identified according to the WHO Child Growth Standards for children under the age of 5 [36].

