### Study design

This is a mixed-method study that involves both qualitative and quantitative methods. In phase one of the study, a qualitative research method will be used while in phase two, a two-armed cluster RCT will be conducted. The primary outcome of the RCT study will be weight-for-age z-score (WAZ), while the secondary outcomes will include height-for-age z-score (HAZ), weight-for-height z-score (WHZ), nutrient intake, diet quality, food security status and nutritional knowledge of mothers. The study population includes 3 to 5 years old children with their mothers who live together in the low-cost PPR flats in Kuala Lumpur. Children aged 3 to 5 years old are recruited because when compared to younger children (<2 years old), older children are at higher risk of undernutrition [32].

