#### Phase 1 (qualitative study)

In the first phase of the study, the identification and classification of families into PD family and NPD family based on the children’s anthropometric measurements will be first carried out. Following that, a qualitative study in the form of focus group discussion (FGD) with semi-structured interviews will be conducted. The inclusion criteria for the participants in Phase I, i.e. the mothers are: Malaysians, above 18 years old with children aged 3 to 5 years old, living in low-cost PPR flats and with a monthly household income of <RM3000. The monthly household income is set at RM3000 because this is the requirement to apply for residing in a public low-cost PPR flat [33]. For a household with more than one child aged 3 to 5 years old, the oldest child will be recruited as the index child. This is because older children have more autonomy in their daily diet, causing them to have higher chances of undernutrition compared to younger children [21]. Mothers whose children are taken care of by other adults will be excluded. Mothers whose children are diagnosed with chronic diseases, under treatment for communicable disease, learning disabilities will also be excluded as these children may have different eating habits and nutritional status, thus possibly contributing to a biased outcome. Apart from that, mothers with overweight or obese children (WHZ > +2SD) will also be excluded. Lastly, mother-child dyads who are involved in any other intervention or clinical research, mothers with mental disabilities, and mothers with low literacy level to fully understand the content of the questionnaires will also be excluded as they might not be capable to follow and involve completely in the present study.

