#### Phase 2 (quantitative study)

A two-armed, cluster randomised controlled trial will be carried out to determine the effectiveness of a nutrition programme. The selection criteria for respondents in this phase will be almost similar to those in Phase 1, except for one criterion related to children. In Phase 2, only undernourished children (either underweight, stunting, or wasting) aged 3 to 5 years old will be recruited to evaluate the effectiveness of the intervention programme in this particular group. The WHO Child Growth Standards for children under 5 will be used to classify children into underweight (WAZ< -2SD), stunting (HAZ< -2SD) and wasting (WHZ< -2SD) [36]. The exclusion criteria in Phase 2 are similar to the exclusion criteria in Phase 1.

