### Implementation of intervention

For the intervention group, a nutrition programme consisting of an education session with peer-led cooking session and rehabilitation session will be provided. The programme will be known as the Nutrition Education and Rehabilitation Session (NERS). It is planned as a 3-month intervention with a total of 12 sessions, each session lasting for two hours for one day in a week, making up a total of four days in one month. The two-hour session consists of half-an-hour of education lesson followed by one and a half-hour of peer-led cooking session. The rehabilitation session will constitute the remaining days before the next education session. The overall education session will be conducted by the researcher. However, the cooking session will be led by volunteers who are recruited from the PD families in the initial stages of the study. Peer-led cooking session will encourage the involvement and active interaction from the volunteers to assist participating mothers in the food preparation processes for child feeding. The participating mothers will need to bring along their undernourished children during this session and feed their children with the prepared meals when they finish cooking. During the process, volunteered mothers from PD family are encouraged to share their knowledges of preparing food and child feeding to the participating mothers to enhance the PD effect. Five to six mothers will be assigned in a group to prepare meals for five to six children. Each group will be assigned with one volunteer to help them throughout the process. Fresh ingredients will be provided. The meal in each cooking session will be prepared according to the pre-planned NERS menu and will be fed as a snack or additional meal to children. This programme will also include a growth monitoring session whereby the participating mothers weigh their children during each session of NERS before the start of the education session. A weighing scale will be provided by the researcher. Mothers will be trained to weigh their children so that they can monitor their children’s nutritional status.

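### WAZ and HAZ are tied to a growth standard for children under 5, but children who enter at 54 months or older pass that age before the last visit

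*Protocol article*

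**What the plan says.** The Study design section makes WAZ the primary outcome and lists HAZ and WHZ among the secondary outcomes.

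- **Standard for the outcome.** The Primary outcome section computes WAZ and identifies underweight children "according to the WHO Child Growth Standards for children under the age of 5". The Secondary outcomes section uses the same WHO standard for HAZ and WHZ.
- **Standard for eligibility.** The Phase 2 section says "The WHO Child Growth Standards for children under 5 will be used to classify children into underweight", and likewise for stunting and wasting.
- **Age at entry.** The Phase 2 section states that "only undernourished children (either underweight, stunting, or wasting) aged 3 to 5 years old will be recruited". The upper limit is not given in months.
- **Visit times.** On the programme, the Implementation of intervention section says "It is planned as a 3-month intervention with a total of 12 sessions". The Measurements section says "All the measurements in the study will be taken at the baseline, immediate post-intervention, and 3-month post-intervention". The visits therefore fall at baseline, about month 3 and about month 6.
- **Choice of child.** Under Phase 1, "For a household with more than one child aged 3 to 5 years old, the oldest child will be recruited as the index child". The Phase 2 section describes its criteria as almost the same as those of Phase 1, apart from one criterion about the child.
- **Missing data.** The Statistical analysis section plans intention-to-treat with multiple imputation where possible.

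**The concern.** WAZ and HAZ are indexed by age, and the named standard stops at the fifth birthday. Children grow older during the six months of follow-up, so some who are within the standard at entry will not be at a later visit. The protocol has no age cap that prevents this and names no other reference for those visits.

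Applied as written, the rule leaves the oldest children with a measured weight and height but no z-score from the stated standard at one or both follow-up visits. The scores would then be either unavailable or taken from outside that standard. If they were coded as missing, they could be swept into the planned multiple imputation, although the child had been weighed. A decision on this made after data collection would be made with outcomes in view.

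**Working it through.** The protocol states no share of children or scores outside the standard, so there is no figure of its own to reproduce. The check derives the share.

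**Inputs**
- Upper limit of the standard: under 5 years, that is, below 60 months (Phase 2; Primary outcome).
- Age at entry: 3 to 5 years, read here as 36 to 59 months because Phase 1 and Sample size estimation speak of under-fives.
- Visits at t = 0, 3 and 6 months (Implementation of intervention; Measurements).
- Enrolled: 82, or 41 per arm (Sampling; Sample size estimation). Allowed non-response: 20%.
- Age distribution: not given. Uniform is assumed first, then varied.

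**Step 1. Entry age at which a child leaves the standard.** A child is outside at visit t if entry age + t ≥ 60 months.
- Month 3: 60 − 3 = 57 months or more at entry.
- Month 6: 60 − 6 = 54 months or more at entry.

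This step needs no assumption about the age distribution.

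**Step 2. Share outside, uniform ages on 36 to under 60 months.** Share = t / 24.
- Baseline: 0 / 24 = 0%.
- Month 3: 3 / 24 = 12.5%.
- Month 6: 6 / 24 = 25%.
- Average over the three visits: (0 + 12.5 + 25) / 3 = 12.5% of WAZ values.

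**Step 3. Counts**

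| Visit | Share | Of 82 enrolled | Of 82 × 0.8 = 65.6 after 20% loss |
|---|---|---|---|
| Baseline | 0% | 0 | 0 |
| Month 3 | 12.5% | 10.2 | 8.2 |
| Month 6 | 25% | 20.5 | 16.4 |

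**Step 4. Sensitivity to the age distribution.** Let age density be linear over the band, with r the ratio of density at the oldest to the youngest age. With u = (age − 36)/24, a = 2/(1 + r) and b = ra, the share is 1 − F(1 − t/24), where F(u) = au + (b − a)u²/2.
- r = 1/2 (younger sample): 8.9% at month 3 and 18.8% at month 6.
- r = 2 (older sample): 16.1% at month 3 and 31.2% at month 6.

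Taking the oldest child moves the sample towards the second case, but only in households with two or more eligible children. The protocol gives nothing from which to size that shift.

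**The case against.** The best counter-argument has several parts.

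- **Five-year-olds.** A reader might take the age range to include children up to 71 months. With uniform ages that puts 12/36 = 33% outside the standard at baseline, 15/36 = 42% at month 3 and 18/36 = 50% at month 6. The documents weigh against this. The Phase 1 definition of a positive deviant family and the Sample size estimation section both speak of under-fives, and entry itself is judged on an under-5 standard. These figures should not be used as the estimate. The criterion is nevertheless not written as below 60 months. If five-year-olds were enrolled, eligibility and baseline would be affected too.
- **All three z-scores.** WHZ is indexed by height, not age, so the count above does not carry over to it.
- **Imputation.** A reader might infer that the plan will impute values for children who were weighed. The Statistical analysis section does not say that a measured weight without a z-score counts as missing. Nor do the documents say what the named software does at the age limit. Imputation is a possibility that the text leaves open, no more.
- **Power.** A reader might subtract 25% from the 41 × 0.8 = 32.8 per arm left after non-response, get 24.6, and call the trial underpowered against its unadjusted 28. That supposes that every affected value is lost and that month 6 is the primary time point. The protocol establishes neither.
- **Bias between arms.** The same age rule and standard apply to both groups, and no mechanism for a differential effect appears in the text.
- **Derivation detail.** The handling of a child who turns five could normally be left to an analysis plan. Here, however, the protocol has itself fixed the standard, the age range and the visit schedule, and the three do not fit together. That part of the objection fails.

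**Conclusion.** The point holds in limited form. The stated standard does not cover every planned WAZ and HAZ value: it fails at month 3 for children aged 57 months or more at entry, and at month 6 for those aged 54 months or more. That follows from the text alone.

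The size depends on assumptions. With entry at 36 to 59 months and uniform ages, about one child in eight is affected at month 3 and one in four at month 6. The plausible ranges are about 9% to 16% and 19% to 31%. Baseline WAZ and eligibility are sound unless five-year-olds are enrolled. The documents support neither a claim of bias between arms nor one of a quantified loss of power. What is shown is that the primary outcome is undefined, under the protocol's own rule, for an age-defined group at follow-up.

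**What to change.** State the upper age limit at baseline in months, say whether the oldest-child rule applies in Phase 2, and adopt one of two options before Phase 2 recruitment.

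1. **Cap entry below 54 months.** All three visits then fall within the stated standard and no derivation rule is needed. The cost is a smaller pool: 6 of the 24 months of the age band are lost. With uniform ages, 24/18 = 1.33 times as many households must be screened. The Sample size estimation section expects about 10 households with undernourished under-fives per flat, so seven flats give about 70 per arm. If all were in the 36 to 59 month band, 70 × 18/24 = 52.5 would remain against the 41 needed. That estimate is not restricted to children aged three and over, so the real margin is probably smaller and should be checked first.
2. **Keep the wider range and fix the derivation.** Name one reference for WAZ and HAZ at visits from 60 months. State that the outcome of a child who was measured is not imputed. Add a sensitivity analysis in all children of weight in kg adjusted for baseline weight, age and sex. The cost is a change of reference at 60 months within some children's series, applied by the same rule in both arms.

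Either option takes a sentence or two of protocol text.

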#### Secondary outcomes

In addition, z-scores for height-for-age (HAZ) and weight-for-height (WHZ) will be calculated. Stunted (HAZ<-2 SD) and wasted (WHZ<-2 SD) children will also be identified based on the WHO Child Growth Standards [36]. Mothers will be interviewed by the researcher on the dietary intake of their children based on the 24-hour dietary recall for three days, including two weekdays and another day on the weekend. For intervention group, the data collection of dietary intake at immediate post-intervention will take place one day after the last session of the program.

Dietary intake will be entered into the Nutritionist Pro^™^ Diet Analysis Software (Axxya, USA) based on the Nutrient Composition of Malaysian Foods database. The adequacy of macronutrient and micronutrient will be determined by referring to the Acceptable Macronutrient Distribution Range (AMDR) of macronutrients and compared with the Recommended Nutrient Intakes (RNI) for Malaysians [42]. Diet quality will also be evaluated using the Healthy Eating Index for Malaysians (HEI) [43]. The possible composite HEI score ranges from 0 (low diet quality) to 100 (good diet quality), in which less than 51% indicates poor diet, 51 to 80% indicates diet requiring improvement, and more than 80% indicates good diet quality [43]. In addition, for the intake of food promoted during the program, mothers will be asked regarding the inclusion of the food in any meals, the frequency and quantity of the foods eaten by their child in the past two weeks.

Nutritional knowledge level of mothers will be assessed by using a questionnaire adapted from a previous study among Malaysian adults [44]. This questionnaire consists of 20 questions on nutritional knowledge related to calorie, carbohydrate, food pyramid, fat, protein, and others. The total scoring will be the total number of correct answers. Based on the percentage of the score, those less than 50% will be classified as unsatisfactory, between 51% to 74.9% as moderate, and more than 75% as satisfactory [44].

Food security status will be determined with the USDA six-item short form of the Household Food Security Survey Module [45]. It is a self-reported tool that contains six questions related to household food security to be answered by mothers. The scoring will be calculated by summing up the total number of affirmative responses. Respondents with less than two affirmative responses will be classified in the “food secure” group while those with two or more affirmative responses will be categorised as “food insecure”. The questionnaire has been previously used in Malaysia [46]. The overview of the study timeline is shown in Fig 1.

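### Collecting the intervention arm's diet recall the day after the last session would, on its plain reading, count a programme-supplied meal in one of three recall days, in that arm only

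*Protocol article*

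**What the plan says.** Under Secondary outcomes, the child's diet is measured by "24-hour dietary recall for three days, including two weekdays and another day on the weekend". The same paragraph adds a timing rule for the intervention group only: "the data collection of dietary intake at immediate post-intervention will take place one day after the last session of the program". The next paragraph adds a question on promoted foods, covering "the frequency and quantity of the foods eaten by their child in the past two weeks".

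Under Implementation of intervention, sessions run weekly ("each session lasting for two hours for one day in a week"), 12 in all. On the food itself, "Fresh ingredients will be provided". Mothers are to "bring along their undernourished children during this session and feed their children with the prepared meals when they finish cooking", and the meal "will be fed as a snack or additional meal to children".

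The Comparison group section describes materials, menus and incentives for completing follow-up, but no meal. Measurements sets the same three time points for both groups. Only the intervention group has a stated day for diet collection. Nothing in the article says that session days are left out of the recall, or that the session meal is removed from the intake data.

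**The concern.** A 24-hour recall describes the day before the interview. An interview one day after the last session therefore describes the session day, which is the one day of that week with a programme meal added to the child's usual food. The comparison arm has no equivalent day. Even if mothers had changed nothing at home, recorded intake at immediate post-intervention would be higher in the intervention arm.

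This matters because Statistical analysis compares energy, macro- and micronutrient intake, diet quality and promoted-food consumption between arms at this time point. The Introduction and Discussion present the programme as working through changed maternal feeding. A difference in diet is the natural evidence for that step, and here part of it could be the last session's meal. If the session meal is not recorded separately at interview, it cannot be taken out afterwards.

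**Working it through.** The article gives no effect size, SD or power for the diet outcomes, so there is no figure of the plan's own to reproduce. The check is about timing and weights.

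**Inputs from the article**
- Recall days: 3 (Secondary outcomes).
- Intervention-arm collection: day +1, with the last session as day 0 (Secondary outcomes).
- Sessions: one per week, so days 0, −7, −14 and so on (Implementation of intervention).
- Supplied meal on each session day in the intervention arm; none in the comparison arm.
- Promoted-food look-back: 14 days.

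**Inputs assumed, because the article does not give them**
- Energy of the session meal: 100 to 400 kcal. The low end allows for a small snack.
- The child attends the last session and eats no less at other times that day.

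**Step 1: weight of the session meal in the recall.** A day +1 recall covers day 0. With weekly sessions, at most one of the three days can be a session day.
- Share of recall days with a supplied meal: 1/3 = 33%.
- Share during the programme: 1/7 = 14%.
- Share after the programme: 0.
- Over-weighting against the programme period: (1/3) ÷ (1/7) = 7/3 = 2.3.

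**Step 2: effect on the 3-day mean.** Bias = meal energy ÷ 3.

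| Assumed meal (kcal) | Added to 3-day mean (kcal/day) | Average over a programme week, meal ÷ 7 (kcal/day) |
|---|---|---|
| 100 | 33 | 14 |
| 200 | 67 | 29 |
| 300 | 100 | 43 |
| 400 | 133 | 57 |

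If no recalled day is a session day, the addition is 0. The same one-third rule applies to each nutrient in the meal. The diet-quality score is a composite, so its shift cannot be computed without the menu. An upward shift is likely, since the materials and recipes draw on national dietary guidance.

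**Step 3: what this could do to a test (illustration only).** Assume further an SD of 250 to 350 kcal for the 3-day mean and no true change in home diet. Take the article's 41 per arm and design effect of 1.27. With SE = SD × √(2/41) × √1.27, the SE is about 62 kcal (SD 250) or 87 kcal (SD 350). By normal approximation, the chance of p < 0.05 rises from 5% to about 7–8% for a 100 kcal meal and about 33–57% for a 400 kcal meal. The width of that range shows how far it depends on the assumptions.

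**Step 4: the two-week question.** Asked on day +1, a 14-day look-back covers days 0 to −13, which includes the sessions on days 0 and −7. Asked on day +7, it covers days +6 to −7 and still reaches both. Asked on days +8 to +14, it includes day 0 only. So in the week after the last session it takes in one or two session meals, depending on exact spacing. Whether a given promoted food was on both menus is not stated.

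**The case against.** **The recalled days are inferred.** The article fixes when collection happens but does not list the three calendar days. The one-day gap might have been meant to start recording after the session. That is possible, but the text does not say so, and collection on day +1 by 24-hour recall covers day 0 in its ordinary sense. What stands is that the point concerns the rule as written and should not be put as an established fact about the data.

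**The meal is part of the programme.** A child who eats it has really eaten it, and the stated objective is the programme's effectiveness in reducing undernutrition. The Discussion also concedes that the design cannot fully attribute the effect to the food provided and the peer educators. This stands in part: the meal is pure bias only if the outcome means home feeding. But even as intake under the programme it is counted at 1/3 instead of 1/7, and the general caveat does not touch recall timing.

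**The reach is narrow.** WAZ is measured by scale. Diet is secondary, and it is measured again at 3 months, when no session falls in either look-back. This stands in full.

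**The two-week question is not tied to day +1.** It comes after the timing rule and carries no date. This stands, so that part is conditional on its being asked in the same week.

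**The comparison arm cannot have a session anchor.** True, and the shared time point is stated. A shared calendar window is still possible.

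**Conclusion.** The point holds in a limited form. On the plain reading of a stated rule, one of three recall days at immediate post-intervention contains programme-supplied food in one arm only. Recorded nutrient intake there is raised by one third of the meal's content, about 33 to 133 kcal/day for an assumed 100 to 400 kcal meal. Diet quality probably moves the same way. The figures assume attendance at the last session and no displacement of other food; absence or displacement would make them smaller. The promoted-food question is affected too if asked within that week.

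A reader might infer more than this, and the documents do not support it:
- That the supplied meal is certain to be in the data. The recalled days are not listed.
- That the bias is a known percentage of intake or makes a false positive likely. Meal energy, usual intake and SD are all absent from the article.
- That the trial cannot separate changed feeding from food delivery at all. The 3-month diet data are free of session meals, and the primary outcome is not measured by recall.

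**What to change.** Choose one of two rules for the recall and state it:

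1. No recalled day is a session day. If each interview covers only the preceding day, the first is held no earlier than two days after the last session. If several days are recalled at one interview, it must be late enough that none of them is the session day.
2. Or keep the timing, record the session meal as a separate entry, and report intake and diet quality with and without it, saying beforehand which is the main result.

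In either case, use the same calendar window for both arms. Word the two-week promoted-food question to count only food eaten outside programme sessions.

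The cost is a shift of about a day under the first rule, or one extra entry on the form under the second, plus the change of wording. The two-week question needs no delay: moving it past the look-back period would require another contact or push back the immediate assessment, and the rewording avoids both.
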